### Duration

Treatment according to randomization starts as soon as possible after allocation, with a maximum of 2 weeks delay. The main outcome assessment will be one year after randomization, but data on sick leave and other social benefits will be followed for at least another year.

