### Inclusion criteria

1) Sick leave due to LBP for 2-10 months

2) At least 50% sickness compensation

3) Both participant and clinician agree that randomization is acceptable

4) Written informed consent from the participant

5) At least 50% employed

6) One of the following ICPC diagnoses: L02, L03, L84, or L86

7) Age between 20 and 60 years

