### Analyses

#### Sample size calculations

The sample size calculations were based on data from Hagen et al. [30] and the transition probabilities calculated for the intervention group in that study. The sample size was based on the transition probabilities at 9 months, where approximately 40% of the individuals had returned to work. Hagen et al. [59] found that the effects were largest for the earlier period after the intervention. This is therefore an argument to use 40% off sick leave at 9 months as the most relevant measure for effect in this study. This was compared to a hypothesized 60% return to work (RR 1.5) as an adequate effect size. The sample size calculations were based on standard formulas for calculating sample size, for studies comparing binomial proportions using the statistical package "R" (Library Hmisc). This may increase the power of the estimates in the analyses, since the simpler method used for the calculation does not include in this issue. All calculations were based on a power of 80% and a significance level of 5%.

Separate sample size calculations for males and females were computed. The total number of individuals should be approximately N = 4*n, where n is the calculated sample size and 4 is the number of arms in the study. The total number of males should be N = 4*65 = 260 and the total number of females N = 4*81 = 324. If we control for gender in the analysis instead of performing stratified analyses, we do not need to calculate separate sample sizes for men and women. The total number of participants should be 97 in each arm (N = 388). These numbers require a multi-centre design.

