### Analysis strategy

#### Primary analyses of efficacy

Sick leave/insurance status will be calculated as risks of shifting between different states of sick leave, disability pension, and recovered. The outcome from the participating clinics will be combined if no gross center effect is found. The analyses will follow the "intention to treat" principle. Per protocol analysis will also be performed. The proportions of participants with a positive primary outcome will also be compared across the treatment groups. If there are significant differences, we will estimate the number of participants that need to be treated in order for one additional participant to benefit (NNT), compared to the least effective therapy. A Cox-proportional hazards model may model the transitions between the different states. Regression models for the transition probabilities will also be performed. Explanatory variables (treatment) and confounders (e.g. age, gender) will be included as in any regression model. Possible changes in diagnosis and other characteristics will be built in. Partial recovery represented by partial sick leave will be accounted for.

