#### Secondary analyses of efficacy

Any significant effects of any of the interventions will be estimated by a standard cost benefit formula [88-90], as used by Hagen et al [59]. Benefits will be measured in terms of increases in the net present social value of production, when intervention causes a reduction in the number of days on sick leave. This is calculated as the product of the treatment effect, i.e. the reduction in sick leave days, and the productivity gains for the society when a person works instead of receiving benefits. For each person the social value of production is based on mean earnings at inclusion in the treatment group. Cost of treatment also includes follow-up at the clinics. Potential differences in treatment costs between the groups, which are related to treatments received independent of the study, will be accounted for by follow-up questionnaires from the participants.

We will also evaluate health complaints/pain and disability as recorded by the questionnaires at 3, 6 and 12 months. Appropriate regression models, based on the distribution for the different outcomes, will be performed, including variables found to be statistically significant predictions.

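### The cost-benefit rule prices every avoided sick-leave day as a day worked, so a move from sick leave to disability pension is credited as production

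*Protocol article*

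**What the plan says.** The protocol article, Secondary analyses of efficacy, says that significant intervention effects will be costed with a standard formula taken from cited sources and used in an earlier study. A benefit arises "when intervention causes a reduction in the number of days on sick leave". The formula reads: "the product of the treatment effect, i.e. the reduction in sick leave days, and the productivity gains for the society when a person works instead". The sentence goes on to name receipt of benefits as the alternative to work. The price of a day comes from earnings: "For each person the social value of production is based on mean earnings at inclusion in the treatment group".

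Three other places bear on the day count:

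- Primary analyses of efficacy models "risks of shifting between different states of sick leave, disability pension, and recovered". Disability pension is therefore neither sick leave nor recovery.
- The same section states: "Partial recovery represented by partial sick leave will be accounted for".
- Duration states that "data on sick leave and other social benefits will be followed for at least another year", so the register data needed to tell these states apart are already planned.

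**The concern.** The two factors of the product do not match. The price is that of a person working rather than drawing any benefit. The quantity it multiplies is the fall in days on one benefit. The two agree only if everyone who leaves sick leave goes to work, and the article's own state model says otherwise.

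An arm in which more patients move to disability pension would then gain economic credit for those moves. An arm that prevents pensions would be under-credited, because the pension days it avoids never enter the count. The cost-benefit part of secondary objective 1 rests on this product, and an economic ranking of the interventions could shift for a reason unrelated to work.

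**Working it through.** **The plan's own figure.** The cost-benefit rule has no numerical result to reproduce. The sample size does, and it supplies the rates used below. For 40% vs 60%, two-sided 5% and 80% power:

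n = [1.960 × √(2 × 0.5 × 0.5) + 0.842 × √(0.4 × 0.6 + 0.6 × 0.4)]² / 0.2² = 96.9, so 97 per arm and 4 × 97 = 388. This agrees with the article.

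**Single patients.** Assume 365 days, a change of state at day 180, and a reference patient fully sick-listed throughout.

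| Path after day 180 | Days credited by the rule | Days worked |
|---|---|---|
| Full return to work | 185 | 185 |
| Disability pension | 185 | 0 |

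The rule cannot tell these two patients apart. Each such pension patient adds 185 / 97 = 1.9 days to the mean of an arm of 97; five add 9.5 days.

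**Arm level.** Inputs:

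- Return to work: 40% in control (Sample size calculations: "40% off sick leave at 9 months as the most relevant measure for effect in this study") and the hypothesized 60% in treatment, taken as constant hazards absent a pension exit. h0 = −ln(0.6)/9 = 0.05676 and h1 = −ln(0.4)/9 = 0.10181 per month.
- Pension: d = −ln(1 − p)/12, with p the 12-month probability absent recovery. The article gives no value, so p is assumed. p = 5% gives d = 0.00427 and p = 10% gives d = 0.00878 per month.
- Horizon T = 12 or 24 months, with 30.44 days per month.

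Formulas:

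- Sick-leave days S = 30.44 × [1 − exp(−(h + d)T)] / (h + d).
- The remaining days, 30.44 × T − S, split between work and pension in the ratio h : d.
- Credited days = S(control) − S(treatment).
- True gain = work days(treatment) − work days(control).

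Because the three states fill the period, credited days = true gain − (pension days in control − pension days in treatment). The error is therefore exactly the between-arm difference in pension days.

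One case in full: 10% pension in control, 5% in treatment, 12 months.

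- Control: S = 252.9, work 97.3, pension 15.0.
- Treatment: S = 206.6, work 152.3, pension 6.4.
- Credited: 252.9 − 206.6 = 46.3. True: 152.3 − 97.3 = 55.0. The gap of 8.7 is the difference in pension days.

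| Assumed pension, control / treatment | T (months) | Credited | True | Error |
|---|---|---|---|---|
| 5% / 5% | 12 | 52.4 | 53.4 | −2% |
| 5% / 5% | 24 | 119.0 | 124.6 | −4% |
| 10% / 5% | 12 | 46.3 | 55.0 | −16% |
| 10% / 5% | 24 | 103.7 | 133.4 | −22% |
| 5% / 10% | 12 | 56.7 | 51.2 | +11% |
| 5% / 10% | 24 | 127.6 | 114.2 | +12% |

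Even equal pension hazards leave a small error, because slower return to work in control leaves more patients exposed to pension.

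**The case against.** **Unseen sources.** The article defers to a cited formula and an earlier study. Either one, or the full protocol, may treat pension days correctly, and the sentence at issue may be only a gloss. That is fair. Still, the article does not leave the effect open: it defines it as fewer sick-leave days, and that is the rule a reader would apply.

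**Intent.** The price refers to benefits in general, which suggests that the authors mean work. This stands as evidence of intent, but it fixes only the value of a day. Nothing in the text removes pension days from the count.

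**Size.** The larger errors need pension rates that differ between arms, and nothing in the article predicts that. This stands.

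**Wrong sign.** A reader might infer that the net benefit could come out with the wrong sign. With no return-to-work effect and assumed pension of 5% in control and 10% in treatment, the rule credits +6.1 days at 12 months while work days change by −1.6. But only significant effects are costed. In the same model at 97 per arm, the standard error of that difference is 18.3 days, so z = 0.33 and the chance of two-sided significance is 6.3%, barely above the 5% false-positive rate; at 24 months it is 7.0%. The article does not say which outcome must be significant, so the case is not excluded, but it does not support a wrong sign as the main risk.

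**Part-time return.** A reader might also infer that part-time return scores no gain, or that an avoided half-graded day is overvalued twofold. Both need graded days to count as whole sick-leave days, which the article never says. The primary-analysis text that partial sick leave is accounted for points the other way. A patient at 50% leave and 50% work for the last 185 days scores 0 under whole-day counting and 92.5 under weighting by degree, and 92.5 is also the work done. Eligibility at "At least 50% sickness compensation" means that graded leave can occur, so the cost-benefit text should state the convention; its silence is not an error.

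**Conclusion.** The point holds for disability pension and, by the same logic, for any other benefit that takes a patient off sick leave without work. The stated rule counts days off sick leave and prices them as days worked, while the article's own state model separates the two.

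Under the planned effect the sign is right in every case computed. The error is slight when pension risks are equal, and it runs from 22% too low to 12% too high when they differ twofold between arms. These figures rest on constant hazards and assumed pension probabilities, so the true size cannot be computed from the article.

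The defect touches only the cost-benefit part of secondary objective 1, within analyses that the article calls exploratory. Primary efficacy and the sample size are unaffected. It deserves correction because the rule is explicit and the remedy is cheap.

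**What to change.** In Secondary analyses of efficacy, replace the fall in sick-leave days, as the treatment effect in the formula, by the between-arm difference in days at work. Define these as days not on sick leave, disability pension or other social benefit, taken from the register data already planned and over the same follow-up. State that graded days are weighted by degree, in line with the primary analysis. Report days on disability pension and on other benefits by arm beside the result.

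The cost is one sentence of wording and a little programming, with no new data collection. The drawback is a less direct comparison with the earlier study whose formula is reused. Keeping the sick-leave-day version as a sensitivity analysis meets that, and the gap between the two versions shows how much of the credited benefit comes from moves to other benefits.

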#### Primary objectives

1) Are BI and CBT, and/or BI and seal oil, more effective than BI alone (BI and placebo) in increasing return to work, reducing health complaints, or both?

2) Are BI and CBT more effective than BI and seal oil, in increasing return to work, reducing health complaints, or both?

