### Hypotheses of efficacy

1) BI and CBT will be superior in return to work and reduction of sick leave

2) BI and seal oil will reduce health complaints, but will not influence return to work or sick leave

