### Randomization

The patients will be randomized, using concealed randomization, to one of the following four treatments; 1) BI only, 2) BI and CBT, 3) BI and seal oil, or 4) BI and soy oil. This is done according to a computer generated randomization list, generated by the trial statistician. The list is stratified by clinic and gender. A central telephone randomization system, as already set up by our research unit will be used. At each of the participating clinics, a research assistant that is not involved in the treatment calls the research unit (Uni Health) to get information on which treatment the patient is randomized to. The research unit receives information about the patient's id number, gender, age, and diagnoses before the treatment allocation is disclosed, ensuring that the sequence is concealed until the intervention is assigned. The allocation code, including details of block size etc. will not be revealed to the researchers or the clinicians until recruitment, data collection, and laboratory analyses are complete. For those patients allocated to nutritional supplementation, the clinics provide blinded boxes, containing capsules with either seal oil or soy oil. All researchers, clinicians, and participants are blinded to treatment allocation of individual participants for the nutritional supplementation. Researchers at Uni Health, the trial statistician, and those assessing the main outcome of the study will be blinded to group assignment. Patients and CBT clinicians will not be blinded to group assignment.

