### Assessment and Procedures

All participants will fill out questionnaires at the clinic immediately before BI. Follow up is conducted at 3, 6, and 12 months after the first session of BI. Data on sick leave will be obtained from the Norwegian National Insurance Administration (see outcome), and will also be collected 24 months after randomization (Figure 1).

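### Covariates for the health-complaint, pain and disability models are chosen by statistical significance, so the adjustment set is open and neither the baseline score nor the randomisation strata are guaranteed

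*Protocol article*

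**What the plan says.** Under Secondary analyses of efficacy the Protocol article states the scope: "We will also evaluate health complaints/pain and disability as recorded by the questionnaires at 3, 6 and 12 months". The method follows: "Appropriate regression models, based on the distribution for the different outcomes, will be performed", and then the covariate rule, "including variables found to be statistically significant predictions". That is the only covariate rule given for these outcomes. No candidate list, threshold or selection procedure accompanies it.

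Other sections bear on it:

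- Assessment and Procedures: "All participants will fill out questionnaires at the clinic immediately before BI". Randomisation comes after BI, so a pre-randomisation score is planned for everyone.
- Randomization: "The list is stratified by clinic and gender".
- Primary analyses of efficacy, for the sick-leave models only: "Explanatory variables (treatment) and confounders (e.g. age, gender) will be included as in any regression model".
- Primary objectives ask whether the treatments are superior "in increasing return to work, reducing health complaints, or both", and Hypotheses of efficacy predicts that "BI and seal oil will reduce health complaints, but will not influence return to work or sick leave".

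**The concern.** A rule that admits covariates because they reached significance leaves the model unknown until the data are in. With two or three outcome domains (depending on whether pain is counted separately) at three visits, there are six to nine models, each of which may end up with its own adjustment set. Treatment estimates at 3, 6 and 12 months would then not be strictly comparable. Nothing requires the choice to be made without sight of the treatment estimate under the competing models.

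The rule also fails to secure the covariates with the best claim to inclusion. The baseline value of the same questionnaire is usually the strongest predictor of its follow-up value. Clinic and gender were used to stratify the list, yet under a significance rule either would drop out wherever its p-value is large.

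The secondary analyses are labelled exploratory, but health complaints appear in both primary objectives and are the only outcome on which seal oil is expected to work. The seal-oil hypothesis therefore rests on these models.

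**Working it through.** **1. The plan's own sample size.** Inputs from Sample size calculations: 40% versus 60% returned to work, 80% power, 5% significance (taken as two-sided).

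n = [1.960·√(2·0.5·0.5) + 0.8416·√(0.4·0.6 + 0.6·0.4)]² / (0.6 − 0.4)² = (1.386 + 0.583)² / 0.04 ≈ 96.9, so 97 per arm. This matches the stated figure and is not in dispute. The article gives no size or precision for the questionnaire outcomes, so 97 per arm is used below.

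**2. What is lost if the baseline score is left out.** In a linear model with baseline-to-follow-up correlation r, adjustment multiplies the residual variance by 1 − r² and the standard error (SE) of the treatment effect by √(1 − r²). The equivalent unadjusted size is 97/(1 − r²). The article gives no r, so 0.3 to 0.7 is an assumption. The reference difference is the standardised difference with 80% power unadjusted: (1.960 + 0.8416)·√(2/97) = 0.402.

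| r | 1 − r² | SE factor with baseline | Equivalent n per arm | Power at 0.402 |
|---|---|---|---|---|
| 0.3 | 0.91 | 0.954 | 107 | 84% |
| 0.5 | 0.75 | 0.866 | 129 | 90% |
| 0.7 | 0.51 | 0.714 | 190 | 97.5% |

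Equivalently, omitting the baseline score makes the SE larger by 1/0.954, 1/0.866 and 1/0.714, that is by about 5%, 15% and 40%.

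**3. What the rule does if the baseline score is a candidate.** Simulation with 97 versus 97, no treatment effect and 4,000 runs per value of r. The candidates are the baseline score and 15 pure-noise variables, each screened singly against the outcome at p < 0.05 without regard to treatment.

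| r | Baseline selected | SE unadjusted | SE, baseline fixed | SE after selection | Type I error after selection |
|---|---|---|---|---|---|
| 0.1 | 29% | 0.143 | 0.143 | 0.142 | 5.0% |
| 0.2 | 80% | 0.144 | 0.141 | 0.140 | 5.6% |
| 0.3 | 98.9% | 0.144 | 0.137 | 0.136 | 5.2% |
| 0.5 | 100% | 0.143 | 0.124 | 0.124 | 5.1% |
| 0.7 | 100% | 0.143 | 0.103 | 0.102 | 4.9% |

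The simulation error on a 5% rate is √(0.05·0.95/4000) = 0.34 percentage points, so these rates are compatible with 5%. The rule misses the baseline score often only at r = 0.1 or 0.2, where little is at stake: the SE factors are √0.99 = 0.995 and √0.96 = 0.980.

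**4. What the simulation does not cover.** The noise candidates were independent and the screening ignored treatment. It says nothing about covariates chosen with the treatment estimate in view, which could raise type I error and which the text does not rule out.

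**The case against.** The strongest reply is that the rule does not cause a loss of precision. It admits significant predictors, nothing bars the baseline score from being one, and at any correlation large enough to matter the score would be selected. This stands. A reader might infer that the plan omits baseline adjustment and so gives away the equivalent of 10 to 93 participants per arm (107 − 97 to 190 − 97). The document does not support that: it describes no model without the baseline score.

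A reader might also infer that the rule inflates type I error or biases the treatment effect. With selection blind to treatment the simulation shows no material inflation. The Randomization section says that the trial statistician and the outcome assessors are blinded. That mitigates the concern but does not settle it, because the same section lets the code be released once recruitment, data collection and laboratory work are complete, which may precede the modelling.

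The article does not say in which data the variables are to be found significant. Predictors of outcome lists predictors from the literature, and Predictions and process of treatment plans separate predictor analyses. Selection in the trial's own data remains the natural reading, but it is a reading.

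Finally, a condensed article may leave its covariate list to a fuller document. The mere absence of a list would indeed be no finding. Here, however, the article states a selection rule, and a fuller plan that followed it would inherit the weakness. The objection that these outcomes are secondary is correct for the main outcome, sick leave, which is untouched. It carries less weight for the seal-oil hypothesis.

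**Conclusion.** The point holds as a weakness in a stated method. The significance rule lets the adjustment set vary by outcome and visit, does not require the choice to be blind to the treatment estimate, and guarantees neither the baseline score nor clinic and gender.

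The loss of precision is conditional. If the baseline score is not offered or not retained, the trial has the precision of 97 per arm where 107 to 190 was available, assuming a linear model and a correlation of 0.3 to 0.7. If it is a screened candidate with a correlation of about 0.3 or more, the loss is negligible and type I error stays near 5% under blind selection. In that case selection gains essentially nothing over a fixed baseline-adjusted model, while the discretion remains. The change should be made. It does not affect the sick-leave analysis.

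**What to change.** In Secondary analyses of efficacy, replace the phrase on significant predictors with:

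*Health complaints, pain and disability at 3, 6 and 12 months are each analysed with the same pre-specified model: treatment, the baseline value of that outcome, clinic and gender; covariates are not selected by significance.*

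Models with significance-selected predictors can be kept as sensitivity analyses, or for the work under Predictions and process of treatment. The new sentence covers only these questionnaire outcomes and leaves the rule on combining clinics in Primary analyses of efficacy as it is.

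The cost is wording only. The baseline questionnaires are completed before BI, and clinic and gender are known at randomisation, so no new data or participants are needed.
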